#### Secondary outcomes

We will address outcomes related to health and behavioural factors including (a) change in depression and anxiety measured using The Mini-International Neuropsychiatric Interview (M.I.N.I.). The outcome is defined as a shift from a M.I.N.I. score indicating depression or generalised anxiety disorder (GAD) to no indication of depression or GAD [28], (b) changes in indicators of general health such as reduction by at least half of sick-leave days and improvements in self-rated health from ‘bad’ or ‘very bad’ to ‘moderate’, ‘good’ or ‘very good’, (c) occurrence of any reported help-seeking for alcohol problems at other treatment providers, such as specialised health care or Alcoholics Anonymous, in the 6- and 12-month intervals.

The M.I.N.I. was developed to accurately detect psychiatric diagnoses according to the *Diagnostic and Statistical Manual of Mental Disorders, version 4* (DSM-IV) and the *International Classification of Diseases, 10th edition* (ICD-10) [28]. The administration time is short and especially suitable for clinical trials and epidemiology studies. The M.I.N.I. is built in modules which can be used separately for rapid screening; this trial employs the modules for depression and GAD.

Self-rated health is used to monitor changes in health over time and has been reported to be a predictor of mortality [29]. The question: ‘How would you rate your overall health’ with the five possible choices ‘very good’, ‘good’, ‘moderate’, ‘bad’, or ‘very bad’ is frequently used within Sweden and the EU.

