#### Exclusion criteria

Clients will be excluded from the study if they:At the time of the call exhibit the features of severe alcohol dependence in need of more intense treatment, as identified by SAH counsellors through a cumulative assessment combining a high score on the AUDIT, psychological comorbidities and a history of treatments for alcohol dependenceUse illicit drugsHave severe mental illness or suicidal intentionReport acute health problems in need of other treatment/medical care

Clients excluded from the study for any of the reasons above, or who wish to terminate participation, will receive counselling according to the SAH current treatment regimen or will be referred to other health care facilities. Concomitant care is permitted during the study period.

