### Data collection

The assessment of clients’ characteristics and of the outcome is conducted using a structured questionnaire with closed-ended response alternatives administered via telephone interviews at baseline, 6-month and 12-month follow-up. The questionnaire includes demographics, the AUDIT scale, self-rated health, sick leave, depression or anxiety symptoms (M.I.N.I.) and help-seeking due to problematic alcohol use. Figure 2 displays the process of recruitment, allocation according to the SPIRIT guidelines.

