#### Statistical analysis

The primary outcome ‘change in AUDIT risk level’ will be analysed as a dichotomous variable where any downward shift (yes/no) from a higher- to a lower-risk level between baseline and follow-up is considered as a clinically meaningful change in drinking habits. The ratio of the cumulative rates of change in the trial groups will constitute the effect measure of the brief, structured intervention versus usual care. General linear models (GLM) will be used to calculate the RR for the outcome event.

Baseline characteristics will be compared between groups in order to detect potential imbalance in predictors of the outcome. If the two groups are not well balanced according to these predictors, multivariable analysis applying logistic regression models will be carried out to estimate odds ratios for the outcome event.

Secondary outcomes (i.e., depression, anxiety, health measures, care seeking) will be analysed using GLM or logistic regression models as described above.

Complementary ‘per-protocol’ and ‘as-treated’ analyses will also be conducted [30]. The ‘per-protocol’ analysis, will only include participants with complete adherence. Complete adherence is defined as: having used the material and received the proactive call (brief, structured intervention); receiving all counselling sessions agreed between the counsellor and the client (usual care). In the ‘as-treated’ analysis, the number of sessions and total duration of the counselling will be considered for each participant, independent of group allocation. These analyses will contribute to the assessment of the effect of the intervention when delivered in standard practice. Possible confounding effects must be carefully monitored in these analyses, since they ignore the random assignment and, therefore, the distribution of baseline risks between participants.

Moderating factors in the analysis include readiness to change, as well as dose-response, i.e., number and length of calls. Further, process data from the records will provide information on the conduct of the proactive calls (adherence).

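### Secondary outcome (c) does not separate new from continuing help-seeking, so care already under way at entry may dilute its risk ratio towards 1 (minor; secondary outcome only)

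*Protocol article*

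**What the plan says.** The protocol article, under Secondary outcomes, defines outcome (c) as "occurrence of any reported help-seeking for alcohol problems at other treatment providers, such as specialised health care or Alcoholics Anonymous". The sentence goes on to limit the event to the two follow-up periods, ending at 6 and at 12 months, but does not tie it to the client's status at entry. The neighbouring outcomes are tied to it. On depression and anxiety the article states: "The outcome is defined as a shift from a M.I.N.I. score indicating depression or generalised anxiety disorder (GAD) to no indication". The sick-leave and self-rated-health outcomes are likewise a reduction and an improvement.

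Nothing under Inclusion criteria or Exclusion criteria bars a client who is already seeing another alcohol-treatment provider. The 12-month wash-out concerns contact with the helpline itself. Past treatment is only one element of the counsellor's overall judgement of severe dependence. The Exclusion criteria section adds: "Concomitant care is permitted during the study period".

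Under Data collection, the questionnaire is "administered via telephone interviews at baseline, 6-month and 12-month follow-up", and its content includes "help-seeking due to problematic alcohol use". A baseline help-seeking item therefore exists. Under Statistical analysis, "Secondary outcomes (i.e., depression, anxiety, health measures, care seeking) will be analysed using GLM or logistic regression models as described above". The analysis described there adjusts for baseline predictors only if the groups turn out to be imbalanced.

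**The concern.** A client who attends Alcoholics Anonymous at entry and simply carries on may be recorded as an event for outcome (c), whichever arm the client is in. Such events say nothing about the difference between the two counselling models, yet they enter the numerator of both risks. A ratio of two risks moves towards 1 when the same amount is added to both.

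The adjustment rule does not help. It is triggered by imbalance, whereas the dilution arises even when pre-existing care is perfectly balanced. What is at stake is the readability of one secondary outcome: a real difference in help-seeking elsewhere could look smaller than it is, or be missed.

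**Working it through.** **Inputs from the article.** Analysed sample of 125 per arm, 5% significance level, 1:1 allocation (Sample size; Methods/design). The article gives no rate or power for outcome (c), so there is no figure of its own to reproduce for this outcome. The power formula can be checked on the primary outcome: 30% against 50%, 125 per arm, two-sided 5%, gives 90.2%, in line with the stated power of more than 90%.

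**Assumed inputs.** New help-seeking among clients not in other care: p1 = 30% (brief arm) and p0 = 15% (usual care), a ratio of 2.0. A share q of each arm is in other care at entry, continues, and reports it.

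**Formulas.** The observed risk in an arm is q + (1 − q)p, so

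RR observed = [q + (1 − q)p1] / [q + (1 − q)p0].

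Power = Φ{(|d| − 1.96·SE0)/SE1}, where d is the difference between the observed risks, SE0 uses the pooled variance and SE1 the unpooled variance.

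**Worked line, q = 10%.** Brief arm 0.10 + 0.90 × 0.30 = 0.370; usual care 0.10 + 0.90 × 0.15 = 0.235; RR = 0.370/0.235 = 1.57. The difference is 0.135, SE0 = 0.0581 and SE1 = 0.0575, so (0.135 − 1.96 × 0.0581)/0.0575 = 0.37 and power is 64%.

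| q | Brief arm | Usual care | RR | Difference (points) | Power, as defined | Power, only those not in care, 125(1 − q) per arm |
|---|---|---|---|---|---|---|
| 0% | 30.0% | 15.0% | 2.00 | 15.0 | 81% | 81% |
| 2% | 31.4% | 16.7% | 1.88 | 14.7 | 78% | 81% |
| 5% | 33.5% | 19.3% | 1.74 | 14.3 | 73% | 79% |
| 10% | 37.0% | 23.5% | 1.57 | 13.5 | 64% | 77% |
| 20% | 44.0% | 32.0% | 1.38 | 12.0 | 50% | 72% |
| 30% | 51.0% | 40.5% | 1.26 | 10.5 | 38% | 66% |

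**Other assumed rates.** With 20% against 10% (ratio 2.0), q = 20% gives 1.29, with power 27% as defined and 51% in those not in care. With 30% against 20% (ratio 1.5), q = 20% gives 1.22. With the direction reversed, 10% against 20% (ratio 0.5), q = 20% gives 0.78. The movement is towards 1 on either side.

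**Partial reporting.** At 30% against 15% and q = 10%, if half of those in care have the event and the other half do not, RR = (0.05 + 0.27)/(0.05 + 0.135) = 1.73 instead of 1.57.

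**What adjustment does and does not repair.** Take q = 20% with balanced strata: 25 clients per arm in care, all with the event, and 100 per arm not in care. The Mantel-Haenszel ratio is (25 + 30)/(25 + 15) = 1.38, the same as the crude ratio. The in-care stratum, however, adds no variance to a stratified test, so that test has the power of the last column (72%, not 50%). Stratification thus recovers the power, and the stratum-specific results show the undiluted ratio. A single ratio standardised over both strata stays at 1.38.

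**The case against.** A reader might infer that pre-existing care is scored as a treatment effect. The article does not support that. Allocation is random, so such care is expected equally in both arms; it makes neither arm look better and raises no risk of a false positive. The absolute difference shrinks only by the factor (1 − q), for instance from 15 to 12 points at q = 20%.

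A reader might also infer that every client in continuing care is certain to be counted. The wording of the questionnaire item is not shown, and it decides whether continued attendance is recorded as help-seeking. Care that ended before the follow-up intervals does not count in any case.

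A third tempting reading is that the trial could wrongly report no shift of burden to other services. The article never gives outcome (c) that purpose. It lists the outcome among health and behavioural factors, and its remark about a less labour-intensive method depends on the brief intervention proving superior.

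Other parts of the case against stand as limits. Any use and new use of other services are both legitimate targets, so the definition is a choice and not an error in itself. The share in care is unsupported in either direction: the Background says most such drinkers never seek health care, and the severe-dependence exclusion probably removes some clients in treatment, whereas the mean AUDIT score of about 21 among first-time callers suggests that some will be in care. Continuation of other care could itself respond to allocation, so the equal addition to both arms is a simplification.

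What survives is that the definition does not separate new from continuing care, that a baseline item exists which could do so, and that adjustment only on imbalance leaves the dilution and the lost power in place.

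**Conclusion.** The concern holds as a dilution problem of unknown size in one secondary outcome. It rests on two conditions that the article leaves open: that some clients are in other alcohol care at entry, and that their continued attendance is reported as help-seeking. If 2 to 5% are in continuing care, the effect is modest (a ratio of 2.0 becomes 1.88 to 1.74, and power falls from 81% to 78 to 73%). At 20 to 30% it is substantial (1.38 to 1.26, power 50 to 38%). These figures all rest on assumed help-seeking rates of 30% and 15%. The primary outcome and the other secondary outcomes are untouched. The point is minor, but worth acting on because the remedy is nearly free.

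**What to change.** Keep any help-seeking as the defined outcome, with three additions:

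1. State whether continuing attendance at a provider already used at entry counts as an event.
2. Always adjust for, or stratify by, baseline help-seeking, whether or not the arms are balanced on it, and show the results by baseline status.
3. As far as the baseline item allows, also report new help-seeking among clients not in other alcohol care at baseline. This is the version that removes the dilution from the ratio.

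No change to eligibility is needed. The costs are a smaller denominator for the third item (100 instead of 125 per arm at q = 20%) and the omission from that version of clients in care who add a new provider, which is why it should stand beside the defined outcome and not replace it. The baseline item may lack the provider detail or look-back period needed for a clean split. Recruitment began in May 2015, so this changes the analysis of one secondary outcome mid-trial; it should be documented and dated before follow-up data are analysed.

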### Sample size

The sample size estimation is based on the primary outcome, i.e., decrease in AUDIT risk category, in a superiority design. Based on a previous observational study of the SAH [12], we estimate that 30% in the usual care group will make a downward shift in AUDIT risk level. We estimate that 300 participants will be recruited to the study, of which at least 250 participants will be included in the analytical sample (125 in each experimental group). Based on the analytical sample the study will have more than 90% statistical power to detect a Risk Ratio (RR) equal to or greater than 1.7 for the alternative counselling (i.e., 50% cumulative rate of change in the brief, structured intervention group) as statistically significant at the 5% level. For a RR of 1.3 the power will decrease to about 50%.

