## Methods/design

The study is designed as a superiority, two-group RCT with follow-up at two time points (6 and 12 months). Clients are individually randomised with a 1:1 ratio to brief, structured intervention or usual care using a computer algorithm and allocation concealment. See Fig. 1 for a schematic overview of the trial. We follow the Standard Protocol Items: Recommendations for Interventional Trials (SPIRIT) Checklist for reporting the study protocol, attached as Additional file 1.

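### The stated power of about 50% for a risk ratio of 1.3 does not follow from the stated inputs: a two-sided 5% test with 125 per arm gives about 32%

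*Protocol article*

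**What the plan says.** All the inputs but one stand in the Sample size section. For the comparator, "we estimate that 30% in the usual care group will make a downward shift in AUDIT risk level". On numbers, "We estimate that 300 participants will be recruited to the study", of whom "at least 250 participants will be included in the analytical sample (125 in each experimental group"). The main claim, made for a risk ratio of 1.7, is "Based on the analytical sample the study will have more than 90% statistical power to detect a Risk Ratio (RR) equal to or greater than" that value. The article equates this ratio with a "50% cumulative rate of change in the brief, structured intervention group". The effect is to be detected "as statistically significant at the 5% level". The next sentence adds: "For a RR of 1.3 the power will decrease to about 50" per cent. The remaining input, equal allocation, is in Methods/design: "Clients are individually randomised with a 1:1 ratio to brief, structured intervention or usual care".

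Neither the Sample size section nor Statistical methods says whether the 5% test is one- or two-sided. Statistical methods describes a superiority design and words the alternative hypothesis in favour of the brief intervention, but declares no one-sided test.

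**The concern.** The two power figures stand next to each other and appear to share a control rate, an analysed sample and a significance level. At 125 per arm the step from 30% to 50% is 20 percentage points and has only a little over 90% power. The step from 30% to 39% is 9 points, less than half of that. A fall to only 50% looked too small.

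This sentence is the article's only statement of how sensitive the trial is to a modest benefit. A reader faced with a non-significant result could use it to judge what the trial might have missed. At a true risk ratio of 1.3, 50% power means missing the effect one time in two. Power of 32% means missing it about two times in three (1 − 0.32 = 0.68).

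**Working it through.** **Inputs.** Usual care p1 = 0.30, analysed n = 125 per arm and α = 0.05 (Sample size); 1:1 allocation (Methods/design). A risk ratio of 1.3 gives p2 = 1.3 × 0.30 = 0.39. Sidedness is not given. Two-sided (z = 1.960) is assumed as the convention, and one-sided (z = 1.645) is shown as the alternative.

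**Formula.** Comparison of two proportions, with p̄ = (p1 + p2)/2:

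- SE0 = √[2 p̄(1 − p̄)/n]
- SE1 = √{[p1(1 − p1) + p2(1 − p2)]/n}
- power = Φ[(p2 − p1 − z·SE0)/SE1]

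**Step 1: the main figure (50% against 30%).** SE0 = √(2 × 0.40 × 0.60/125) = 0.0620 and SE1 = √[(0.21 + 0.25)/125] = 0.0607.

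- Two-sided: Φ[(0.20 − 1.960 × 0.0620)/0.0607] = Φ(1.295) = 90.2%.
- One-sided: 94.7%.

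Both satisfy the claim of more than 90%. The article's 1.7 is a rounding of 0.50/0.30 = 1.67.

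**Step 2: the second figure (39% against 30%).** SE0 = √(2 × 0.345 × 0.655/125) = 0.0601 and SE1 = √[(0.21 + 0.2379)/125] = 0.0599.

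- Two-sided: Φ[(0.09 − 1.960 × 0.0601)/0.0599] = Φ(−0.465) = 32.1%.
- One-sided: Φ[(0.09 − 1.645 × 0.0601)/0.0599] = Φ(−0.149) = 44.1%.

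**Step 3: does the choice of formula matter?** Two-sided at 39% against 30%: unpooled 32.4%, log risk ratio 31.8%, arcsine 32.3%, exact enumeration of the Pearson test 32.7%, continuity-corrected 27.5%. One-sided, the same variants lie between 38.9% and 44.4%. None reaches 50%.

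**Step 4: does rounding of the risk ratio matter?** If 1.3 stands for 1.33 (40% against 30%), then SE0 = 0.0603 and SE1 = 0.0600.

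| 125 per arm, 5% level | 39% v 30% (RR 1.30) | 40% v 30% (RR 1.33) | 50% v 30% (RR 1.67) |
|---|---|---|---|
| Two-sided | 32.1% | 38.1% | 90.2% |
| One-sided | 44.1% | 50.5% | 94.7% |

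Even at 1.349, the largest ratio that rounds to 1.3, two-sided power is only 41.0%. No rounding of the ratio brings a two-sided test to about 50%.

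**Step 5: does the sample matter?** With all 300 analysed (150 per arm), 39% against 30% gives 37.4% two-sided and 49.8% one-sided. The article, however, bases its power statement on the analytical sample, not on the number recruited.

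**Step 6: what does the planned sample deliver, two-sided?**

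- Risk ratio 1.4 (42% against 30%): 50.7%.
- Risk ratio 1.58 (47.4% against 30%): 81.0%.
- For 50% power at a risk ratio of 1.3, about 215 per arm (430 analysed) would be needed, against 250 planned.

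**The case against.** The strongest reply is that one consistent basis reproduces both sentences. The article writes 1.67 as 1.7, so it may equally write 1.33 as 1.3. With 125 per arm and a one-sided 5% test, 40% against 30% gives 50.5% and 50% against 30% gives 94.7%. The directional alternative hypothesis makes a one-sided test a possible reading. This stands as far as it goes: 32% depends on an assumption about sidedness, and the shortfall ranges from nothing to 18 points according to the reading.

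It also rules out a stronger inference that a reader might draw, namely that the two figures must have been computed on different bases, for example one on 250 and the other on all 300 participants. The 90.2% match does not prove that, because more than 90% is an inequality that 94.7% also meets.

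The reply does not rescue the sentence as printed. It needs two things that the article does not state: a one-sided test at the 5% level, and a ratio other than exactly 1.3. A directional hypothesis is not a declaration of a one-sided test. Without that test, power is 38% even at 40% against 30%.

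It can also be said that the figure is secondary, and that the article already admits low power at 1.3. That is fair, and it limits the weight of the point, but the number is still one that readers may rely on.

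**Conclusion.** The point holds in a conditional form. On the article's stated inputs and a two-sided 5% test, power for a risk ratio of 1.3 is about 32%, so about 50% overstates it by about 18 percentage points. Across the readings considered at 125 per arm the range is 32%, 38%, 44% and 50.5%. Only the last agrees with the article, and it combines an undeclared one-sided test with a ratio of 1.33.

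A reader might infer that the trial is undersized or that its main power claim fails. The documents do not support this: the claim for a risk ratio of 1.7 reproduces, and the planned 300 recruited and 250 analysed do not depend on the second figure. The fault lies in the stated sensitivity to a modest effect and should be corrected, but it does not threaten the design.

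**What to change.** State whether the 5% test is two-sided or one-sided, give the two proportions behind the 1.3, and restate the power to match. If the test is two-sided, a suitable sentence is: with 125 per group and a two-sided 5% test, power is about 32% for a risk ratio of 1.3 (39% against 30%), about 50% for 1.4 and about 80% for 1.58. If a one-sided test was meant, say so and give 44% for 39% against 30%, or 50.5% for 40% against 30% with the ratio written as 1.33.

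The cost is one sentence and, if the test is two-sided, a less favourable figure. Enrolment, design and analysis do not change.

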### Recruitment

The recruitment procedure will be activated when a new client first calls the SAH.

#### Procedure of recruitment

The procedure for participant recruitment was developed in collaboration with responsible staff at the SAH. Before conducting the trial, the feasibility of the procedure was tested in a pilot study.

After assessing eligibility, the counsellors briefly inform eligible clients about the study and ask if they would agree to receive further information. In case of interest, counsellors:Ask in which mode clients wish to receive written information (i.e., e-mail, mail or web)Provide information about the baseline interview and randomisation procedure and ask for the clients’ preferred time of the interviewRegister contact information and the client’s willingness to participate in the studyEnd the counselling session and terminate the call as soon as possibleSend out the required written information

Within five working days, interested clients are contacted by an interviewer, who completes the following sequence of tasks:Ascertains that the client received sufficient information about the studyAsks for formal consent to participate to be recorded in the client’s recordConducts the baseline interviewOpens a sequentially numbered, sealed envelope containing the results of the randomisation algorithm and communicates the group assignment to the clientSchedules the proactive call for all participants randomised to the brief, structured intervention and upon agreement for participants randomised to usual careInforms the research coordinator of the allocation of each participant

The coordinator records the allocation in the study-specific database and creates an electronic prompt for the next step (e.g., proactive call) in the client record at the SAH.

